# Platelet-Rich Plasma Versus Saline for the Treatment of Vulvar Lichen Sclerosus: Protocol for a Randomized Controlled Trial

**DOI:** 10.2196/68871

**Published:** 2025-09-03

**Keywords:** regenerative medicine, vulvar dermatoses, female sexual health, autologous therapies, clinical trial protocols, women’s health research

## Abstract

**Background:**

Vulvar lichen sclerosus (LS) is a chronic relapsing dermatosis commonly affecting the anogenital region in postmenopausal women, though it can affect people of any age and sex. The current gold standard treatment is lifelong topical steroid application to reduce symptoms and prevent the progression of disease, causing irreversible architectural change to the vulval tissue. LS is associated with decreased quality of life and increased risk of vulvar neoplasia. Alternatives to current treatments are highly desired by both clinicians and patients. Platelet-rich plasma (PRP) is an autologous blood product containing high concentrations of platelets and growth factors and is hypothesized to promote wound healing. PRP has been reported to improve symptoms of LS in several case reports and uncontrolled trials.

**Objective:**

This study aims to evaluate the efficacy of PRP versus saline injections to improve the clinical signs and symptoms of LS.

**Methods:**

This is a protocol for a 12-month, single-center, parallel-group, double-blind, randomized controlled trial evaluating the efficacy of PRP for LS compared to saline. Adult female patients with biopsy-proven LS who are otherwise in good health but are nonresponders to topical steroid treatment prior to inclusion are eligible for the trial. A total of 68 participants will be randomly allocated via a random number generator to receive either PRP or saline injections to areas of the vulva with LS. All participants will be blinded to the intervention received. Participants will be followed up with assessments of clinical LS signs, subjective symptom scores, and quality of life questionnaires by blinded assessors at 4 timepoints: baseline, 6 weeks, 6 months, and 12 months. The primary outcome is the clinical scoring system for LS—the total LS score.

**Results:**

Recruitment commenced in May 2020 and concluded in November 2023. This study closed in September 2024 due to slow recruitment. Data are being analyzed in 2025, and results are expected to be published in late 2025.

**Conclusions:**

This study will evaluate the safety and efficacy of PRP injections compared to those of saline injections for the treatment of vulvar LS, potentially providing a novel therapeutic option for patients who do not respond to topical steroids.

**Trial Registration:**

Australia and New Zealand Clinical Trials Registry ACTRN12618001321235p; Universal Trial Number: U1111-1207-4893; anzctr.org.au/Trial/Registration/TrialReview.aspx?id=375536

**International Registered Report Identifier (IRRID):**

DERR1-10.2196/68871

## Introduction

### Background

Vulvar lichen sclerosus (LS) is a chronic autoimmune dermatosis with a complex and multifactorial etiology [1,2]. In females, LS typically affects the anogenital region, including the vulva, perineum, and anus, but extragenital involvement occurs in 6%-20% of the patients [3,4]. The characteristic signs of LS are patches of discolored white skin, and the typical symptoms are intense itching, burning, and pain [5-7], which can contribute to significant distress and discomfort. Over time, chronic changes to the architecture of the vulva can occur, such as agglutination of the labia and narrowing of the introitus [3]. Additionally, LS is associated with an increased risk of vulval intraepithelial neoplasia and vulvar squamous cell carcinoma, with an estimated malignant transformation risk of approximately 4% to 6% [8,9]. The incidence of LS has been estimated at 22 per 100,000 woman-years in population studies [10], and it accounts for about 1.7% of the referrals to general gynecology clinics [11,12].

There is no cure for LS, and the current mainstay of therapy is topical corticosteroid application [3]. The goals of the therapy are symptom relief and improving the quality of life, preventing the progression of disease to alter the architecture of the skin, and reducing the risk of neoplasia [3].

Platelet-rich plasma (PRP) is an autologous platelet concentrate, which contains the platelet-derived growth factor, transforming growth factor, and epidermal growth factor, and it is hypothesized to promote wound healing and tissue regeneration [13,14]. It has yielded positive results in orthopedic, reconstructive surgery, dentistry, dermatology, and musculoskeletal medicine [15-18]. PRP has been studied as a treatment for LS [19], but issues with small sample sizes, heterogenous study methodologies, short-term follow-up, and the use of unvalidated outcome measures are the limitations that have prevented the recommendation of PRP use in clinical practice [13]. In the context of LS, PRP may exert therapeutic effects through its anti-inflammatory and immunomodulatory properties. Growth factors such as transforming growth factor-β and platelet-derived growth factor found in PRP can modulate the immune responses and promote tissue remodeling. These effects may reduce local inflammation, improve dermal regeneration, and help restore the structural integrity of vulvar tissues affected by LS. Therefore, this trial has been designed as an adequately powered, placebo-controlled randomized study to evaluate the safety and efficacy of PRP in LS by using validated outcome measures.

In contrast to prior studies [20,21], this trial addresses these limitations by employing a randomized, double-blind, placebo-controlled design with an adequately powered sample size. It also utilizes validated clinical and patient-reported outcome measures, including the clinical scoring system for LS, Dermatology Life Quality Index, and Australian Pelvic Floor Questionnaire, with a planned 12-month follow-up. These methodological strengths are designed to provide robust evidence on the efficacy and safety of PRP for LS.

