#### Secondary Outcome Measures

Secondary outcome measures will compare changes in the subjective assessment scores over time within each group and between groups. Participants will complete the Australian Pelvic Floor Questionnaire and Dermatology Life Quality Index at each assessment appointment to evaluate changes in the subjective disease burden. The Australian Pelvic Floor Questionnaire is a validated self-administered questionnaire assessing pelvic floor symptoms, including bladder, bowel, prolapse, and sexual function symptoms, as well as symptom severity and impact on quality of life [23]. The Dermatology Life Quality Index is a validated tool assessing quality of life impairment for people experiencing inflammatory skin conditions, and a change in the score of at least 4 points is considered clinically significant [24]. A Visual Analogue Scale will be presented to participants at each assessment to record the severity of their symptoms. Participants will be asked to indicate their level of distress in relation to 2 symptoms: pruritus and dyspareunia.

The additional secondary outcomes are safety and adverse events of receiving the treatment. Autologous PRP has an advantageous safety profile due to the utilization of the patient’s own blood, which minimizes the risk of adverse events or autoimmune reactions [25]. In a pilot study undertaken by the principal investigator, all participants (n=28) reported minimal to mild pain in the 24 hours following the procedure [20]. There were no reported cases of infection, bleeding, hematoma, or other adverse effects. Adverse events will be monitored immediately after receiving the treatment, and at each assessment appointment, participants will be asked if they experienced any adverse events in the preceding period. Any adverse effects will be recorded and reported to the ethics committee.

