#### Sample Size and Power Calculations

Sample size calculations are based on the pilot study on 28 patients [20], in which 80% of the participants treated with PRP experienced an improvement in their symptoms. Assuming a difference of 30% between PRP and normal saline at 12 months, an α risk of 5%, and a power of 80%, a sample size of 31 participants for each group is required. Assuming that 10% of the participants withdraw or are lost to follow-up, a sample size of 34 participants for each group is required or a sample size of 68. The pilot study used subjective symptom improvement as its primary outcome, whereas this trial’s primary outcome is the LS clinical score, an objective physician-rated measure. Although these outcomes differ, symptom improvement in the pilot study was used as a surrogate to estimate a conservative effect size for this study, given the lack of prior data on LS clinical score changes with PRP. This study will also evaluate secondary outcomes, including subjective symptom scores, allowing for comparisons between subjective and objective measures.

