## Results

Recruitment for the trial commenced in May 2020 and concluded in November 2023. The study is closed as of September 2024 due to slow recruitment. A total of 34 participants were recruited. Data analysis is being performed in 2025, and the study results are expected to be published in late 2025.

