### Limitations

As a study protocol, there are several anticipated limitations to consider. This trial is being conducted at a single private clinical center, which may limit the generalizability of findings to other settings, particularly public hospitals or international populations. Although the study is powered to detect a significant difference between groups, the modest sample size may not capture rare adverse events or allow detailed subgroup analysis. Additionally, although outcome assessors and participants are blinded, the treating investigator must remain unblinded for procedural reasons, introducing a potential risk of bias. Lastly, although validated tools such as the clinical scoring system for LS and quality of life measures are employed, patient-reported outcomes are inherently subjective and may be influenced by expectations, even in a placebo-controlled setting.

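### The power claim in the Background covers safety, but only symptom improvement was sized, and the caveat about rare adverse events is too narrow

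*Protocol article*

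**What the plan says.** The Background presents the trial as the answer to earlier small studies: "this trial has been designed as an adequately powered, placebo-controlled randomized study to evaluate the safety and efficacy of PRP in LS". The next paragraph, after listing the design features, adds: "These methodological strengths are designed to provide robust evidence on the efficacy and safety of PRP for LS".

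The status of safety is set out under Secondary Outcome Measures: "The additional secondary outcomes are safety and adverse events of receiving the treatment". No expected event rate, difference from saline, margin or interval width is attached to it. The same section reports that the 28 pilot participants had minimal to mild pain in the first 24 hours and no infection, bleeding, hematoma or other adverse effect.

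Sample Size and Power Calculations starts from the pilot study, "in which 80% of the participants treated with PRP experienced an improvement in their symptoms", assumes a 30% difference from saline at 12 months, and arrives at 31 per group, or 34 per group after 10% dropout. No adverse-event quantity enters.

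The Limitations section says the study is powered to detect a difference between groups, and adds that "the modest sample size may not capture rare adverse events or allow detailed subgroup analysis". The Results section reports: "A total of 34 participants were recruited", half of the planned 68.

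**The concern.** Calling a trial adequately powered for a purpose implies that its size was chosen, or at least checked, for that purpose. For safety the article shows neither. The claim is a positive statement that the article's own sizing section does not support, so it is not a detail left to an analysis plan that is not shown.

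The caveat in the Limitations section does not repair this. It admits blindness to rare events only, so a reader would assume that anything more frequent is covered. Whether it is covered can be calculated.

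What is at stake is how far the safety conclusion can go. Safety compared with saline is part of the goal under Study Aims and returns in the Conclusions. Apart from transient pain, the pilot suggests a sparse record of events. A sparse record from a trial described as adequately powered for safety carries more weight with readers than the numbers justify. The results are still to be published, so the wording can be corrected.

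**Working it through.** **Inputs from the article.** Improvement of 80% on PRP, a difference of 30 percentage points (read as 80% against 50%), α 5%, power 80%, 31 per group, 34 per group after dropout (Sample Size and Power Calculations); 1:1 allocation (Randomization and Blinding); 34 recruited in total (Results).

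**Assumptions.** An even split of the 34 recruited, 17 per arm, because the split is not given. Adverse-event rates are illustrative, because the article gives none.

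**1. The article's own figure.** Two proportions, pooled variance:
n = [z_α·√(2·p̄·(1−p̄)) + z_β·√(p1(1−p1) + p2(1−p2))]² / (p1−p2)², with p̄ = 0.65.
- One-sided 5%: [1.645·√0.455 + 0.842·√0.41]² / 0.09 ≈ 30.2, so 31. This matches.
- Two-sided 5%: z_α = 1.960 gives about 38.5, so 39.
- Dropout: 31/0.9 = 34.4 and 31·1.1 = 34.1, against the stated 34.

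The 31 is therefore an efficacy figure, and every term in it is an improvement rate. Whether it is adequate for efficacy is a separate matter.

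**2. What zero events would exclude.** For zero events in n participants, the exact (Clopper-Pearson) two-sided 95% upper limit is 1 − 0.025^(1/n).
- n = 34: 1 − 0.025^(1/34) = 10.3%.
- n = 17: 1 − 0.025^(1/17) = 19.5%.

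**3. Chance that an event type never appears on PRP,** (1−p)^n.

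| True rate | n = 34 | n = 17 |
|---|---|---|
| 5% | 0.95^34 = 17% | 0.95^17 = 42% |
| 10% | 0.90^34 = 3% | 0.90^17 = 17% |

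**4. Power to show an excess over saline.** Fisher's exact test, two-sided 5%, by summing the binomial probabilities of all significant tables.

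| PRP against saline | 34 per arm | 17 per arm |
|---|---|---|
| 20% against 5% | 31% | 12% |
| 30% against 5% | 72% | 35% |
| 30% against 10% | 44% | 19% |
| 40% against 10% | 77% | 39% |
| 50% against 10% | 94% | 63% |

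With no events on saline, significance needs at least 6 of 34 (18%) or 5 of 17 (29%) on PRP. By the formula in step 1 with two-sided α, 80% power for 20% against 5% would need 76 per arm.

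**The case against.** The strongest reply is that this is ordinary practice: trials are sized on efficacy and describe safety. The article lists safety as a secondary outcome, shows openly what was sized, and warns that rare events may be missed. The Objective and the Study Design section name efficacy alone, and Study Aims and the Conclusions speak of assessing safety without a power claim. All of this is true, and sizing on efficacy is no design defect. What remains is the sentence in the Background that attaches adequate power to safety, and a caveat that stops at rare events.

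Three stronger readings are tempting and are not supported.

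- *That neither sample size can show or exclude even common adverse events.* This goes too far. At 34 per arm a 10% event would be missed altogether with only 3% probability, zero events would exclude rates above 10.3%, and power is 72% for 30% against 5% and 94% for 50% against 10%. The article does not define common, so the point has to be made in rates.
- *That the figures at 17 per arm show the design statement to be false.* The sentence is about design, so the planned 34 per arm is the test, and it fails there for moderate excesses. The figures at 17 come from the early closure and an assumed even split. They bear on the caveat and on what can be concluded now.
- *That the investigators will present a clean record as proof of safety.* Nothing in the article says so; it is an inference about readers. Since every pilot participant reported minimal to mild pain, a record with no events at all is not even the expected result if such pain is counted.

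It is also fair to say that adverse-event tables usually belong to the analysis plan. Their absence here is not the finding.

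**Conclusion.** The statement is wrong as written. The article claims adequate power for safety, while its only calculation concerns symptom improvement and no safety rate or precision was set. At the planned size the trial could detect only large excesses over saline: power is 31% for 20% against 5%, and a record with zero events of a given type would still fit true rates up to 10.3%. At the recruited size these become 12% and 19.5%. Events at 10%, and even approaching 20%, are not rare in any usual sense, so the caveat in the Limitations section is too narrow.

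The lack of any safety sizing can be read directly from the article. The magnitudes depend on the illustrative event rates and, for the recruited sample, on an even split. The efficacy analysis and the conduct of the trial are unaffected; what changes is how much the trial may say about safety.

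**What to change.** - **Background:** remove safety from the power claim and from the promise of robust evidence, and describe the safety evaluation as descriptive. This should not be worded so as to endorse the power for efficacy, which needs its own review.
- **Limitations:** replace the reference to rare adverse events with the rates that the recruited sample cannot exclude, using one interval convention. With 17 on PRP, for example, zero events leaves an exact two-sided 95% upper limit of 19.5%. Use the actual number per arm once it is known.
- **Results report:** give the number and proportion of participants with each adverse event per arm, with exact 95% intervals. State that neither safety nor safety equal to saline will be concluded from few or absent events or from a nonsignificant difference.

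The cost is wording in two sections and intervals in one table, with no further participants or procedures. The safety claim becomes less favourable.

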### Study Aims

The goal of this study is to assess the safety and efficacy of autologous PRP injections for the treatment of vulvar LS compared to saline injections.

## Methods

### Study Design

This is a double-blind, parallel-group, placebo-controlled, randomized trial. The purpose of the trial is to evaluate the efficacy of PRP as a treatment for vulvar LS compared to saline. The trial is conducted at a single center—FBW Gynecology Plus in Adelaide, Australia.

### Study Population

Adult female patients formally diagnosed with LS are the target population for this study.

#### Inclusion Criteria

Patients will be eligible if they remain symptomatic from vulvar LS despite topical steroid treatment or if they are intolerant of or unable to use topical steroids.

#### Exclusion Criteria

The exclusion criteria were as follows: (1) patients on antiestrogens, (2) patients on systemic immunosuppressants such as prednisolone, methotrexate, or biologics that were taken within 12 weeks of commencing the trial, (3) patients with gynecological or breast cancers, (4) patients with autoimmune disorders who require antiplatelet medication, except Sjogren syndrome and LS, (5) patients who are immunocompromised or who have uncontrolled malignant disease, (6) patients diagnosed with lichen planus, psoriasis, candidiasis, vulvar intraepithelial neoplasia, or vulvar carcinoma, (7) patients with vulvodynia, (8) patients with acute vaginal infection or systemic infection, (9) patients on antiplatelet medications, including aspirin, (10) patients without capacity to give consent, and (11) patients who are uncooperative, known to miss appointments, are unlikely to be compliant, or unable to attend regular scheduled visits.

#### Recruitment

Recruitment will be conducted over a minimum of 18 months to allow for adequate enrollment and potential participant withdrawal. Eligible patients presenting to the clinic with a confirmed clinical diagnosis of LS during routine consultations will be systematically screened for study inclusion according to the predefined eligibility criteria. All eligible patients will be informed about the study and invited to participate in a standardized manner (Multimedia Appendix 1). Patients who express interest will have an appointment scheduled with a clinical investigator who is a gynecologist to assess their eligibility and confirm their enrollment. The purpose of this appointment is to obtain consent from the patient, record demographic data, schedule all treatment and assessment appointments, and assign the patient with a unique study identifier number.

#### Withdrawal

Participants who do not complete the full treatment regimen and/or do not complete all assessments will be withdrawn from the study to ensure the quality of data analysis. The reasons for the withdrawal will be documented if provided. Any participant who withdraws from the study will be advised to consult with their referring physician to continue conventional treatment for their LS.

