### Ethical Considerations

This study has received ethics approval from Bellberry Human Research Ethics Committee (2017-07-546-PRE-1, PRP4LS) on October 2, 2018. All participants provided written informed consent prior to enrolment, as documented in the participant information sheet and consent form (Multimedia Appendix 1). The trial will be conducted in accordance with the National Health and Medical Research Council National Statement on Ethical Conduct in Human Research (2023) incorporating all updates [1]. Participants were informed that their participation was voluntary, that they could withdraw from the study at any time without any impact on their ongoing medical care, and that they could choose whether their data collected up to the point of withdrawal could be retained or removed from the study dataset. All data were deidentified prior to analysis. Participant identifiers were replaced with unique study codes, and no information that could directly identify participants was included in the research database. Participant details were stored in an electronic medical record system, and the deidentified study dataset was kept in a password-protected Excel file located on a secure server at the study site. Only authorized study personnel had access to identifiable data, and all records were handled in accordance with applicable privacy and data protection regulations. No monetary payment was provided to participants for their involvement in the study. Participants were required to arrange their own travel to appointments; however, travel vouchers were available upon request. Findings from this trial will be reported in accordance with the CONSORT (Consolidated Standards of Reporting Trials) statement and disseminated to the scientific community via peer-reviewed journals, conferences, medical education sessions, and patient information sessions.

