### Statistical Analysis

All analyses will be conducted using SPSS software (IBM Corp). We will perform analyses using the intention-to-treat principle. Outcomes will be compared within groups over time and between groups at baseline, 6 weeks, 6 months, and 12 months. Baseline characteristics will be summarized using descriptive statistics, and a comparison of the 2 treatment arms will be assessed by 1-way analysis of variance or 1-sided *t* test for continuous variables or nonparametric alternatives if data are not normally distributed. The Shapiro-Wilk test will be used to assess if data are normally distributed. For all tests, a significant level of α=5% is applied. The analysis of changes compared to the baseline will test the null hypothesis that there is no difference between the 2 timepoints. Further analyses between the groups will test the null hypothesis that there are no differences between the 2 groups at one timepoint. Missing value analysis will be performed, and missing values will be imputed using expectation maximization. Analyses will be conducted in line with the intention-to-treat principle, which will be compared to per-protocol analyses.

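### The withdrawal rule for any missed treatment or assessment conflicts with the intention-to-treat analysis, the imputation and the per-protocol comparison that the same protocol promises

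*Protocol article*

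**What the plan says.** The protocol article addresses incomplete participants in three places.

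- **Withdrawal** (under Study Population): "Participants who do not complete the full treatment regimen and/or do not complete all assessments will be withdrawn from the study". The purpose given is better data for the analysis. On reasons it adds: "The reasons for the withdrawal will be documented if provided".
- **Statistical Analysis**: "We will perform analyses using the intention-to-treat principle", and later "Analyses will be conducted in line with the intention-to-treat principle, which will be compared to per-protocol analyses". On missing data: "Missing value analysis will be performed, and missing values will be imputed using expectation maximization".
- **Ethical Considerations**: participants were told that they could withdraw at any time and that "they could choose whether their data collected up to the point of withdrawal could be retained or removed from the study dataset".

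The Treatment Appointments and Assessment Appointments sections define completion: two treatments (baseline and 6 weeks) and four assessments (baseline, 6 weeks, 6 months, 12 months). The primary outcome is the change in LS clinical score at the three post-baseline timepoints.

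**The concern.** The rule is mandatory, one missed visit is enough to trigger it, and its stated reason is analytic rather than safety or consent. Intention-to-treat serves the opposite purpose: everyone randomised is kept in the comparison, whether or not she completed treatment or follow-up.

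Incompleteness is plausibly related to outcome, for example through lack of relief or discomfort after the first injection. If incomplete women drop out of the comparison, the arms are no longer the randomised groups and the estimated difference can move in either direction. If they are kept but not followed, the 6- and 12-month scores that the primary outcome needs do not exist and must be modelled. With 34 recruited, about 17 per arm, one woman is about 6% of an arm (1/17 = 5.9%).

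**Working it through.** **1. The sections side by side, on the two possible readings**

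| | Withdrawn women leave the dataset | Scores up to withdrawal are kept |
|---|---|---|
| Who is analysed | Women with both treatments and all four assessments | All randomised, less any removal requests |
| Intention-to-treat vs per-protocol | Essentially the same set, so the comparison is empty | Different sets, so the comparison has content |
| Imputation | No missed visits to impute, at most isolated items | Has work to do, because withdrawal creates the gaps |
| What is lost | All data from incomplete women | Every score after the missed treatment or visit |

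On the second reading, expectation maximization needs missingness to be at random given what was observed. A woman who misses the whole 6-week appointment and is withdrawn has only a baseline score to condition on. Reasons are recorded only when offered, so the assumption is hard to examine.

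**2. The plan's own figure**

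Inputs from Sample Size and Power Calculations: 80% improvement on PRP, a difference of 30% (read here as 80% vs 50%; the 50% is inferred, not stated), α = 5%, power 80%.

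n = [z_α √(2·0.65·0.35) + z_β √(0.8·0.2 + 0.5·0.5)]² / 0.30²

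- With z_α = 1.645 (one-sided) and z_β = 0.842: (1.110 + 0.539)² / 0.09 ≈ 30.2, so 31 per arm, as stated.
- With a two-sided α the same formula gives 39. That is a separate matter and does not affect this point.
- Allowance for loss: 31/0.9 = 34.4, against the stated 34 per arm.

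The 80% vs 50% reading is therefore a fair basis for an illustration, and the planned loss is 10%.

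**3. Effect of a completers-only comparison**

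Assume a fraction d of one arm leaves, all non-improvers, and any loss in the other arm is random. An arm with 50% true improvement then shows 0.50/(1 − d).

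| d in the affected arm | Apparent rate | False difference if both arms are truly 50% | Apparent difference if truly 80% vs 50% and the loss is in saline |
|---|---|---|---|
| 10% (planned) | 0.50/0.90 = 55.6% | 5.6 points | 80 − 55.6 = 24.4 points |
| 20% | 0.50/0.80 = 62.5% | 12.5 points | 80 − 62.5 = 17.5 points |
| 30% | 0.50/0.70 = 71.4% | 21.4 points | 80 − 71.4 = 8.6 points |

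**4. How much loss the rule itself could cause**

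The documents give no missed-visit rate. If each of the three post-baseline visits is missed independently with probability m, the rule withdraws 1 − (1 − m)³.

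- m = 3%: 8.7%
- m = 5%: 14.3%
- m = 10%: 27.1%

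A 5% rate per visit would already exceed the planned 10%.

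**The case against.** The strongest defence is that the sections can be read together. The Withdrawal section does not say that scores already collected are deleted. Ethical Considerations allows data up to withdrawal to be retained, and Statistical Analysis states intention-to-treat twice. On that reading visits stop, earlier scores stay, later ones are imputed, and the per-protocol set holds the completers. Analysis sets may also be defined in fuller documents that are not shown.

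Much of this stands. A reader might infer that the promised intention-to-treat analysis has simply become a completers analysis with nothing to impute. The text does not establish that; it holds on one reading only. But the data-quality rationale points towards exclusion, and the retention choice is described for women who decide to withdraw, not explicitly for those withdrawn by rule. The milder reading still loses later primary-outcome scores. No analysis plan can recover scores that were never collected.

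Two other inferences go too far:

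- **Size.** If half the non-improvers in a 50% arm left, the figures would be about 17 points of false difference, or a fall from 30 to 13. That means 25% loss in one arm, all non-improvers, well above the planned 10%.
- **Closure.** Recruitment ended in November 2023 and "The study is closed as of September 2024 due to slow recruitment". A reader might conclude that a known number of late entrants missed 12 months and were withdrawn. No enrolment dates are given, any count would need an assumed accrual pattern, and the rule does not mention closure.

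Nor does the article report that anyone was withdrawn under the rule or that any data were removed.

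**Conclusion.** The concern holds as a conflict within the document. The withdrawal rule and the analysis section need reconciling, and either way of applying the rule harms the randomised comparison: by exclusion, or by ending collection of later primary-outcome scores.

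At the planned 10% loss, concentrated in one arm and entirely among non-improvers, a completers-only comparison is off by about 5.6 points: a false 5.6 under no effect, or 24.4 instead of 30 if the loss is in saline. Larger selective loss biases it more; loss unrelated to outcome would not bias it. These figures assume 80% vs 50% and the binary improvement scale of the sample size calculation. The primary outcome is a 0–12 score, so they show direction and order of size and do not predict this trial's bias.

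**What to change.** Before the primary comparison is run, reconcile the Withdrawal and Statistical Analysis sections as follows:

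1. State that a missed treatment or visit does not remove a participant from the analysis.
2. Define the primary analysis set as all randomised participants in their allocated arm, using every score collected, except where a participant asked for her data to be removed. Report how many did so, by arm.
3. Confine the completer rule to the per-protocol set.
4. Report by arm how many women were withdrawn under the rule, at which visit, and the reasons where known. If any 12-month scores are missing because the study closed, report them separately as administratively missing.

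The cost is a few sentences and a check that all scores in the participant folders are in the analysis dataset. No new participants or visits are needed. Because the study is closed, rewording the rule cannot recover follow-up that was not done; the change concerns the analysis set and reporting only.
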